## Measures to minimize bias: Randomization and blinding

Randomization will be completed after study enrollment and will be 1:1 ATI to control (maintain ART). Image reviewers and biopsy reviewers will be blinded to randomization assignments until all 12 participants have completed the protocol and results have been analyzed as described in statistical considerations. The imaging reviewer is blinded as part of the determination of whether this study will be repeated. The biopsy reader is blinded to minimize bias in choosing which “hot” or “cold” nodes to biopsy. A Clinical Center (CC) staff radiologist who is not the blinded radiologist will review the PET/CT scans as they come in for clinical review and identification of sites to biopsy. As the ATI group will have three scans and the non-ATI group will have two scans, scans will be de-identified, and the first two scans will be used for discrimination of ATI vs. non-ATI to preserve blinding.

Randomization will be done by the Biostatistics Research Branch of the National Institute of Allergy and Infectious Diseases (NIAID). The randomization code will be maintained by the Biostatistics Research Branch on secure servers. The randomization code will be shared with all study staff except the blinded imaging and biopsy reviewers during the course of the study. Randomization will be performed *via* block randomization.

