#### ATI or continue ART phase

After the baseline imaging visit, participants will be randomized 1:1 to either continue their ART regimen or undergo ATI, to begin 2 weeks (±3 days) after baseline. This interim serves two purposes: (1) to give ATI participants time to recover so they can be biopsied from the same site again if indicated, and (2) for those on ATI who take NNRTIs, to switch to a protease inhibitor or an integrase inhibitor–based regimen to ensure that the washout period of ARV drugs is roughly equal. The study team will work with the participant's regular care team to adjust ART regimens as needed and oversee the ATI. If necessary to ensure a safe discontinuation of ART, the interval between baseline and ATI initiation may be lengthened up to 8 weeks. ATI participants will have a second set of imaging and biospecimen collection 7–13 days after starting ATI. A biopsy reviewer who is blinded to cohort assignment (ATI or continuing ART) will review the whole body PET/CT images and determine what sites to biopsy.

Participants on ATI will have weekly study visits to monitor HIV symptoms, viral load, and CD4 count. When the participant meets a restart criterion, including reaching 90 days of interruption even if no other criterion is met, they will resume their ART at the next weekly visit. This ART restart visit will include a research blood draw. As this blood draw is critical to the study goals, participants who do not return for their ART restart visit will be replaced. Participants who withdraw prior to achievement of ART resumption criteria will similarly be replaced. However, their data will be kept as it can be used in the PET/CT and biopsy timing analyses. They will be advised on resuming their ART at home and will be followed for safety.

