## Discussion

HIV is controlled but not cured by combination antiretroviral therapy, and the mechanisms of HIV persistence remain poorly characterized. ATI studies have been useful in investigating the events in HIV rebound (71–77); many ATI studies analyze HIV present in plasma or in peripheral blood mononuclear cells. Most replication takes place in tissues, however, and HIV reactivation in tissues during ATI has not been well-studied. This protocol will allow us to explore utility of PET for identification of areas of high FDG uptake indictive of increased metabolic activity. By biopsying both FDG hot and FDG cold areas, we will be able to characterize these regions and investigate HIV replication during treatment interruption. One hypothesis is that PET SUV correlates with HIV viral RNA in biopsy of those regions and that lymph nodes with high SUV have higher viral RNA compared with areas with low SUV within a patient. If this is true, PET may be useful for identification of HIV infected cell populations, as well as monitoring response to cure strategies.

A randomized design was selected for this study to account for natural variation that might be seen in FDG uptake over time and to test the hypothesis that ATI engenders changes in FDG uptake not seen in patients who continue ART. Neither of these considerations could have been addressed without inclusion of the control ART continuation group. The possibility of doing only the ATI group, with each participant's baseline scan serving as their own control, was explored. Natural longitudinal variation in FDG uptake could, however, confound this approach. As Pfaehler and coworkers have reported, FDG PET uptake may be subject to variation from a number of potential sources (78, 79). Randomization to ATI vs. continuation of ART was necessary to optimize the balance of additional known and unknown confounders. The data generated, using rigorous uptake quantification, will also serve as an assessment of natural variation in FDG uptake over time, which will have general utility for FDG uptake studies.

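### As worded, the plan permits the randomization code itself, and so upcoming assignments, to reach all unblinded staff while enrolment and replacement are still under way

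*Protocol article*

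**What the plan says.** All references are to the protocol article.

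Under *Measures to minimize bias: Randomization and blinding*, the NIAID Biostatistics Research Branch performs the randomization. It is blocked, and no block size is given. On custody of the code: "The randomization code will be maintained by the Biostatistics Research Branch on secure servers". The next sentence is: "The randomization code will be shared with all study staff except the blinded imaging and biopsy reviewers during the course of the study". Earlier in the section, the reviewers are said to be blinded to randomization *assignments*, which is a different term from the *code*.

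On timing, the same section places randomization after enrolment. *ATI or continue ART phase* adds: "After the baseline imaging visit, participants will be randomized 1:1 to either continue their ART regimen or undergo ATI". *Study design* leaves participants and study team unblinded, apart from an imaging reader and a biopsy reader. The *Discussion* explains why the trial is randomized at all: "Randomization to ATI vs. continuation of ART was necessary to optimize the balance of additional known and unknown confounders".

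**The concern.** Blinding and allocation concealment are separate protections. An open-label trial gives up the first, but it can keep the second if nobody who decides whether and when a person enters can foresee the next assignment. Having an independent branch randomize and hold the code serves that purpose. Sharing the code itself with nearly all staff during the study would undo it.

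Several decisions come before assignment and leave room for judgement: discretionary exclusions, the order in which eligible people are enrolled, and the conduct of baseline procedures. The arms also differ in burden. Under *ATI or continue ART phase*, the regimen switch for NNRTI users is described only for those going on to ATI. Someone who knew the next assignment could, without any ill intent, defer one person or bring another forward. The balance of known and unknown confounders claimed in the *Discussion* would then no longer be assured by design.

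**Working it through.** **The plan's own figure.** The article gives no figure for concealment. Its figure for the randomized comparison, in *Sample size justification*, is a one-tailed Fisher p of 0.04 with 6 per arm. With one misclassification in each arm this reproduces: [C(6,5)·C(6,1) + C(6,6)·C(6,0)] / C(12,6) = (36 + 1)/924 = 0.040. Neither the defect nor the fix changes it.

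**Step 1: what is shared.** Two consecutive sentences use the same term. The object that the branch maintains is the randomization code, and the object shared with staff is the randomization code. The article has another term, assignments, and does not use it here. No sentence makes sharing per participant or conditional on randomization.

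**Step 2: when.** Sharing is during the course of the study. In that time, 12 people are enrolled from up to 50 screened (*Screening*). ATI participants who withdraw before meeting the ART resumption criteria, or who miss the restart visit, are replaced (*ATI or continue ART phase*). The whole study may be repeated with new participants (*Resume ART phase or continue ART phase*).

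**Step 3: what is decided before assignment.** Six *Exclusion criteria* expressly rest on investigator judgement: drugs that interfere with FDG, poorly controlled diabetes, comorbidity raising ATI risk, substance abuse or psychiatric illness, drug resistance, and any other contraindicating condition. Enrolment order, baseline imaging and baseline biopsies also come first. Randomizing after these steps conceals the assignment only if it is not already known.

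**Step 4: how much the list adds.** With the full code, 12 of 12 upcoming assignments are known. The fair comparator is the same trial with the list withheld but past assignments visible, since the team is open label. Assume a fixed block size 2b that staff know. The article does not give the size, so the sizes below are assumptions, all dividing 12.

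- Expected assignments known with certainty, out of 12: 12/(b + 1).
- Expected share guessed correctly, always guessing the arm with more places left in the block: {b + ½[2^(2b)/C(2b,b) − 1]} / 2b.

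| Block size | Certain, of 12 | Best-guess accuracy |
|---|---|---|
| 2 | 12/2 = 6.0 | (1 + ½[4/2 − 1])/2 = 75% |
| 4 | 12/3 = 4.0 | (2 + ½[16/6 − 1])/4 = 71% |
| 6 | 12/4 = 3.0 | (3 + ½[64/20 − 1])/6 = 68% |
| 12 | 12/7 = 1.7 | (6 + ½[4096/924 − 1])/12 = 64% |

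Full enumeration of the possible blocks gives the same values. Disclosing the list therefore raises the number known for certain from between 1.7 and 6.0 to 12.

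**Step 5: leverage of one participant.** One person is 1/6 = 17% of an arm. The rules in *PET/CT and biopsy timing justification* can turn on one ATI participant: 6/6 with a 3-fold RNA increase moves imaging earlier and 5/6 does not; 1/6 moves it later and 2/6 does not by that criterion. This shows sensitivity to who is in the arm. It is not an estimate of bias.

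**The case against.** The strongest reply is that the sentence is only the converse of the blinding rule. The people excluded from the code are the same reviewers who are blinded to assignments, so the authors may have meant that everyone else may know each arm once it is assigned. An open-label interruption trial needs that, because visits and scans differ by arm. Central randomization after enrolment and baseline imaging fits this reading, and an article may leave release procedures to the full protocol. This stands as a plausible account of the intent. It does not rescue the wording, which makes a positive statement about the code and sets no limit on it.

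The reply also limits the harm. Every participant must be willing to interrupt ART, and the exclusions for ATI risk apply to both arms. Table 1's primary endpoint and the hot-versus-cold comparison rest on tissue changes or contrasts within participants, and the timing rules are counts among ATI participants. The reader's classification of arms is blinded and uses de-identified first and second scans. No route from steering to a changed result is demonstrated.

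Several stronger readings are tempting and are not supported:

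- *That concealment is removed.* This is certain only if the code means the forward list and staff receive it before enrolling.
- *That predictability rises from 50% to 100%.* Half is the wrong starting point in an open-label blocked trial, as Step 4 shows.
- *That 50 − 12 = 38 people could be steered.* Fifty is a ceiling on screening, and those not enrolled may simply be ineligible.
- *That staff who schedule visits should not know the arm.* After randomization they must.
- *That block sizes must vary.* With 12 participants this is a trade-off, because it can threaten the planned 6:6 split.

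**Conclusion.** The point holds as a defect in a stated rule. Followed literally, the sentence lets upcoming assignments be known to the people who make discretionary eligibility and enrolment decisions, and no other section supplies a safeguard. The size is 12 of 12 assignments foreseeable, against 1.7 to 6.0 of 12 with the list withheld. It rests on two assumptions: that *code* means the forward list, and, for the comparator, that the block size is fixed, known to staff and between 2 and 12. The article does not name who enrols or confirms eligibility; they are covered only as part of all study staff. If the authors meant disclosure of each assignment once made, there is no loss of concealment beyond what an open-label blocked trial already carries, and the sentence should say so. Either way the text needs the same correction. No bias in any result has been shown.

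**What to change.** Replace the sentence with wording to this effect: the randomization code and block sizes remain with the Biostatistics Research Branch; each participant's assignment is released singly to the unblinded team only after eligibility is confirmed, the participant is enrolled, and the baseline PET/CT and biopsies are complete; the imaging and biopsy reviewers remain blinded as already planned.

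The cost is small: one sentence, and a release step per participant by the group that already holds the code. Sample size and analysis are unchanged. The sequence matches the one the article describes. Baseline biopsies fall within 5 days of imaging and ATI starts nominally at 14 days, so release after the biopsies leaves 14 − 5 = 9 days at the nominal schedule. The change will not make assignments unpredictable, since past assignments stay visible and the randomization is blocked; it takes away the certainty that comes from holding the list.

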### Biospecimen evaluations

Biospecimen collection includes both required and optional samples. A summary of planned specimen collection and analyses to be conducted with these specimens is outlined in Table 2.

### Genetic/Genomic analysis

Somatic genetic testing may be conducted on blood, biopsy, and/or CSF samples. Genetic tests include HLA typing, interferon variant analysis, and mitochondrial DNA analysis.

The following may be done on samples collected under this study:

In order to understand molecular evolution of HIV over time in infected individuals, HIV DNA and/or RNA will be sequenced. It will include both whole genome sequencing (9–10 kb) and HIV env sequencing (1.2 kb).Transcriptomic (sequencing from mRNA) analyses of cells.Limited genomic DNA sequencing to identify targeted polymorphisms. The limited genomic DNA sequencing may also include epigenetic analyses.Whole genome or whole exome sequencing will not be done under this protocol. All participants will be offered co-enrollment in the NIAID Centralized Sequencing Protocol (NIH IRB# 17-I-0122), but this is optional and not a condition of participation on this study.

## Design and statistical considerations

### Sample size justification

We will use a sample of size *n* = 12, with 6 participants randomized to the ATI group and 6 to the control group. A blinded PET/CT reader will attempt to correctly classify participants into their respective groups.

We determined the sample size of 12 participants (six on each arm) to allow for the blinded imaging reader to make an incorrect assignment and still obtain a significant *P*-value (*p* = 0.04) using a 1-tailed Fisher exact test and an alpha of 0.05. If we had used 10 participants (5 in each arm) instead of 12, then one incorrect assignment would yield a Fisher's exact test *P*-value of 0.103.

### Estimating the probability that an ATI participant has at least one productive hot spot

The probability p that an ATI participant has at least one hot spot that corresponds to a potential site of HIV replication or immune activation after ART discontinuation (we will use the term “productive hot spot”) will be estimated using a Bayesian procedure. Further details can be found in Supplementary material S1.

### Comparison of PET hot and cold biopsy samples for ATI participants

This will be restricted to ATI participants with abnormal hot spots; cold spots will be identified for comparison. HIV DNA values for hot and cold samples on each participant will be ranked and participant mean rank differences computed. A permutation test will be used to determine whether differences between cold and hot spots are beyond what would be explained by chance. Further details can be found in Supplementary material S1.

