**Anticipated results:**

We anticipate that PET standardized uptake values (SUV) will correlate with HIV viral RNA in biopsies of those regions and that lymph nodes with high SUV will have more viral RNA than those with low SUV within a patient. Individuals who undergo ATI are expected to have diverse viral populations upon viral rebound in lymphoid tissue. HIV populations in tissues may initially be phylogenetically diverse after ATI, with emergence of dominant viral species (clone) over time in plasma. Dominant viral species may represent the same HIV population seen before ATI.

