Upon introduction of ART, new virus transmissions to uninfected cells are effectively blocked. Viral RNA levels in blood decline as new cells are not being infected and infected cells are eliminated, either by direct viral killing or by immune-based mechanisms to eliminate virus-infected cells. Viral RNA levels in plasma decline as infected cells are eliminated by multimodal decay kinetics. A sharp initial decline of 10- to 100-fold in the first 1–2 weeks of therapy corresponds to loss of cells with a relatively short half-life (1–2 days) (5). This initial decline is followed by a second phase decline, with a characteristic half-life of 2–3 weeks, corresponding to the loss of longer-lived cells, including macrophages and long-lived CD4+ T cells. Within 1–6 months, viral RNA levels decline to a level less than that quantifiable by commercial HIV RNA detection. Use of sensitive single-copy HIV RNA detection assays has revealed HIV RNA levels undergo a third phase decline with a half-life of ~39 weeks, likely corresponding to long-lived cell compartments. Analysis of individuals undergoing long-term ART has revealed persistent viremia with no further decay detected after 3 to 4 years (6).

HIV-infected cells persist during therapy and are readily detectable using sensitive techniques. Viral RNA levels decline a median of 17,000-fold after introduction of ART, but cell-associated viral DNA declines only 10- to 30-fold, suggesting a substantial population of remaining virus-infected cells (7, 8). These quantitative studies only measure the presence of HIV DNA and do not detect or quantify levels of replication-competent virus. Other detailed studies have consistently demonstrated that the level of replication-competent HIV is only a small fraction (1–3%) of the total number of infected cells, as demonstrated by Chun et al. and Bruner et al. (9–12). HIV-infected cells are present in peripheral blood as well as diverse anatomic compartments, including secondary lymphoid organs [lymph nodes, spleen, and gut-associated lymphoid tissue (GALT)], central nervous system (CNS), and renal tissue, all of which may represent viral sanctuaries.

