## Objectives and endpoints

Our primary objective is to assess the correlation of FDG-PET activity with changes in HIV RNA in lymphoid tissues before and after ATI. Secondary objectives will evaluate correlation of FDG-PET with HIV RNA in other compartments, as well as characterize changes in both DNA and RNA. Objectives and endpoints are summarized below in Table 1.

**Table 1 T1:** Study objectives and endpoints.

**Objectives**	**Endpoints**	**Justification for endpoints**

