**Primary**		
To evaluate if changes in glucose metabolism (as measured by FDG-PET SUV) correlate with changes in levels of HIV RNA in lymphoid tissue before and after ATI	Proportion of participants who have a 3-fold increase in HIV RNA levels in tissue sites identified by imaging as having increased SUV on FDG-PET as defined below	There are limited data on sensitivity of FDG-PET to detect HIV-infected cell populations during ATI. We will determine utility of this approach for investigating HIV persistence in people living with HIV

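### The article's only hot-versus-cold test ranks HIV DNA, but the within-patient hypothesis it should serve is stated in HIV RNA

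*Protocol article*

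**What the plan says.** All references are to the Protocol article.

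- **The test.** The section *Comparison of PET hot and cold biopsy samples for ATI participants* sets the population ("This will be restricted to ATI participants with abnormal hot spots; cold spots will be identified for comparison"), the variable ("HIV DNA values for hot and cold samples on each participant will be ranked and participant mean rank differences computed") and the method ("A permutation test will be used to determine whether differences between cold and hot spots are beyond what would be explained by chance"). Further detail is deferred to Supplementary material S1, which is not shown.
- **The hypothesis for the same contrast.** The Abstract, under *Anticipated results*, expects that "lymph nodes with high SUV will have more viral RNA than those with low SUV within a patient". The *Discussion* repeats it as one hypothesis, that "lymph nodes with high SUV have higher viral RNA compared with areas with low SUV within a patient".
- **The primary objective and endpoint.** *Objectives and endpoints* states: "Our primary objective is to assess the correlation of FDG-PET activity with changes in HIV RNA in lymphoid tissues before and after ATI". The endpoint in Table 1 is: "Proportion of participants who have a 3-fold increase in HIV RNA levels in tissue sites identified by imaging as having increased SUV on FDG-PET".

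The article gives no reason for using DNA in the hot/cold test and describes no parallel test on RNA.

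**The concern.** The hypothesis and the test make the same contrast, hot against cold nodes within a patient, but on different analytes. The two are not interchangeable, and the article's own background explains why. The *HIV persistence* section notes that DNA measurements do not quantify replication-competent virus, which it puts at 1–3% of infected cells. The same section says that most infected cells carry defective proviruses.

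The protocol asks whether FDG-avid sites reflect HIV replication, immune activation or both. A DNA contrast can depart from the RNA hypothesis in either direction:

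- Hot nodes could produce more viral RNA while holding about the same amount of HIV DNA as cold nodes. The RNA hypothesis would then be true, and the DNA test would have nothing to find.
- Hot nodes could hold more infected cells without more viral RNA. The DNA test could then be positive while the RNA hypothesis is false.

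At stake is whether a headline anticipated result gets a prespecified test. With at most the six planned ATI participants in the comparison, choosing or swapping the analyte after seeing the data would undermine the p-value.

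**Working it through.** **Step 1. The plan's own figure.** The only p-values in *Sample size justification* are for the blinded reader's classification, using a one-tailed Fisher exact test with one participant misassigned in each arm:

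- 6 per arm: (6×6 + 1)/C(12,6) = 37/924 = 0.0400, stated as 0.04.
- 5 per arm: (5×5 + 1)/C(10,5) = 26/252 = 0.1032, stated as 0.103.

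Both reproduce. Neither involves the hot/cold test, so the sample size does not depend on its analyte.

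**Step 2. Does any described analysis compare RNA in hot with RNA in cold sites?**

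| Where | Quantity | Comparison | Hot vs cold on RNA? |
|---|---|---|---|
| Table 1, primary endpoint | 3-fold rise in tissue HIV RNA | Proportion of participants, at sites with increased SUV | No, no cold-site comparator |
| Table 1, secondary endpoint 1 | HIV DNA levels, integration sites | Clonal distribution across biopsy sites and fluids | No, DNA |
| Table 1, secondary endpoint 2 | DNA and RNA sequencing characteristics | Against change in SUV | No, sequence features rather than RNA level |
| Table 1, exploratory endpoint 2 | DNA, RNA and immune markers by site | Serves the objective on CSF, semen and vaginal secretions | No, other compartments |
| *Resume ART phase or continue ART phase*, initial data analysis | Total tissue HIV RNA by PCR | Between arms, and over time within arm | No |
| *PET/CT and biopsy timing justification* | 3-fold RNA rise; reader recognition | Counts among ATI participants | No |
| *Estimating the probability…* (productive hot spot) | Bayesian probability; analyte not named in the article | Per ATI participant | No contrast described |
| *Comparison of PET hot and cold biopsy samples…* | HIV DNA | Hot vs cold within participant | Contrast yes, RNA no |

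Only the last row makes the hot/cold contrast, and it uses DNA. The first row cannot substitute: an RNA rise of the same size in hot and cold nodes alike would count as success on the primary endpoint.

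**Step 3. Does changing the analyte cost anything in attainable significance?** Assume hot and cold labels are permuted within participant, with no ties. With h hot and c cold samples in each of k participants, the smallest one-sided p is (1/C(h+c, h))^k.

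- One hot and one cold each: (1/2)^6 = 0.0156 for 6 participants, (1/2)^5 = 0.031 for 5, (1/2)^4 = 0.0625 for 4.
- Two hot and two cold each: (1/6)^2 = 0.028 for 2 participants, (1/6)^3 = 0.0046 for 3.

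These floors depend on the number of participants and samples (about 2–5 biopsies per scan), not on the analyte. They are therefore the same for RNA as for DNA where both are measured. Missing or tied RNA values would raise them.

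**The case against.** **The primary objective is already analysed in RNA.** This stands. A reader might infer that the trial's central claim is never tested, but the document does not support that. The primary objective concerns change in SUV against change in tissue RNA before and after ATI, and it has an RNA endpoint. RNA is also compared between arms and over time. A hot/cold comparison at one time point would not by itself answer a before-and-after objective.

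**No decision depends on this test.** This also stands. Repeating or retiming the study depends on reader classification and the 3-fold RNA rise. Nothing in the article says that a null DNA test would lead to PET being declared uninformative.

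**DNA is relevant.** True. The Abstract's *Discussion* names identification of HIV-infected cells as an aim, and DNA levels at biopsy sites are a secondary endpoint. That is a reason to keep the DNA test, but it leaves the RNA prediction without one.

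**Supplementary material S1 may settle it.** S1 may name RNA or both analytes. But the article does not merely omit the variable; it names DNA. If S1 says RNA, the article needs correcting. If S1 says DNA, the mismatch stands.

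**Two tempting ways to put a number on the loss do not work.**

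- The *HIV persistence* section reports a median 17,000-fold fall in viral RNA after starting ART, whereas "cell-associated viral DNA declines only 10- to 30-fold". Those figures describe starting ART. They do not describe tissue about 10 days after stopping it, or differences between nodes, so their ratio does not measure any loss in this test.
- One might argue that if DNA does not change during ATI, the test has no power beyond its alpha. The test compares nodes with each other, not one node over time. Hot and cold nodes may differ in DNA even if neither changes.

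**Conclusion.** The point holds as a mismatch between one stated hypothesis and its test. The article predicts more viral RNA in hot than in cold nodes within a patient. Its only hot-versus-cold test ranks HIV DNA, and no other described analysis supplies the RNA contrast. The planned test is informative about HIV DNA burden but does not test the RNA prediction.

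Its reach is limited to this secondary contrast. It does not affect the primary endpoint, the sample size of 12 or the timing rule. No loss of power can be calculated from the document. The conclusion rests on the article's wording alone, since S1 could not be checked; either way the article's text needs correcting or reconciling.

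**What to change.** Before analysis:

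1. In *Comparison of PET hot and cold biopsy samples for ATI participants*, name tissue HIV RNA, normalised to CD4 cells as in Table 2, as the variable for the permutation test. Specify the second set of biopsies, taken 7–13 days after ATI starts.
2. Keep the same test on HIV DNA as a separately labelled analysis of infected-cell burden.
3. State which of the two is the main analysis.
4. Align Supplementary material S1 with this wording.

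The cost is small. Tissue HIV RNA from lymph node biopsies is already planned, so the change adds one analysis and no procedure, participant or visit. RNA will be available only where biopsy material is sufficient, as Table 2 notes, so the RNA test may rest on fewer samples than six participants would suggest.
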